## Abstract

**Introduction:**

Autism Spectrum Condition (ASC) is characterised by difficulties in social communication and interaction, which may pose significant challenges to daily functioning throughout life. While current diagnostic methods for ASC often rely on measures based on subjective reports, there is a growing need for objective, quantifiable measures to support current clinical assessment of ASC. Eye-tracking technology records eye and gaze movements in real time and provides a direct and objective method for assessing social attention. Integrating eye-tracking within virtual reality (VR) environments presents a novel approach for capturing gaze behaviour in dynamic, ecologically valid social scenarios. This study aims to investigate whether VR-based eye information can reveal group differences in gaze behaviour between autistic adults and neurotypical controls in simulated social interactions.

**Methods:**

This case-control study will include 140 adults diagnosed with ASC and 50 neurotypical controls, matched by age and gender. Participants will engage in six VR-based social scenarios, which vary in social complexity and the presence of non-social distractors. Eye information will be measured using eye-tracking technology integrated into a head-mounted display. Gaze behaviour will be analysed through fixation-based metrics on parameters including number of fixations, mean fixation time, and dwell time, on predetermined Areas of Interest.

**Analysis:**

Statistical analyses will assess between-group differences in gaze behaviour as well as correlations between gaze metrics and clinical measures of social functioning, social cognition and symptom severity.

**Discussion:**

This study utilises VR-based eye-tracking to investigate novel paradigms for assessing gaze behaviour in ASC in immersive, interactive environments and aims to advance the current understanding of visual social attention in ASC. Positive outcomes from this study may support further research into VR-based eye-tracking to supplement existing clinical assessment methods.

## Introduction

*Autism Spectrum Disorder* (ASD) is a neurodevelopmental condition characterised by impairments in social communication and interaction, alongside restricted and repetitive behaviours and interests and deviant reactivity to sensory stimuli [1,2]. In line with international recommendations, this paper will adopt the term *Autism Spectrum Condition* (ASC) and employ identity-first language (*autistic adults*), though it is acknowledged that preferences regarding terminology vary among individuals and communities [3–5]. Similarly, individuals without a developmental or current psychiatric diagnosis will be referred to as *neurotypical* individuals.

For autistic individuals, social-communicative impairments may present as challenges in social-emotional reciprocity, non-verbal communication, and difficulties forming relationships, often resulting in significant psychosocial distress and impacting daily functioning, occupational performance, and overall quality of life [6–8]. The global prevalence of ASC is estimated to be between 1–2%, where adults constitute a growing proportion of this group [8,9]. Being a neurodevelopmental condition, this increase in adult prevalence is unexpected, and several hypotheses have been proposed to account for the development, including revised and improved diagnostic criteria, increased awareness, and a growing recognition of compensatory strategies (*camouflaging*) that may have masked symptoms and resulted in children and adolescents going undiagnosed [8–12]. As a result, “a lost generation” has formed, comprised of those individuals who remain undiagnosed or misdiagnosed into adulthood [13].

Diagnosis in adulthood presents unique challenges. As a neurodevelopmental condition, ASC requires that symptoms be present from childhood, meaning diagnosis is contingent on accurate retrospective reporting, often from family members, which may neither be accurate nor accessible [13]. Additionally, many individuals who remain undiagnosed into adulthood do so as a result of acquiring compensatory strategies or camouflaging behaviours to mask their autistic traits in social settings, further complicating diagnostic processes [13,14]. Current diagnostic methods are also reliant on subjective measures such as self-reports and clinical observations, which may be susceptible to bias, potentially leading to misdiagnosis [15]. Objective behavioural markers, such as gaze behaviour, may have the potential to support current clinical assessment methods for ASC.

Gaze behaviour provides a valuable behavioural measure in understanding social cognition. The development of eye-tracking technology has enabled the quantification of gaze patterns, and the study of how individuals allocate visual attention. In humans, gaze functions as a signal to modulate communication, evident in the attentional bias known as *visual social allocation*, where neurotypical populations tend to direct attention towards socially salient features, such as eyes and faces [16,17]. Conversely, atypical gaze patterns may indicate aberrant social perception, reflected as impairments in social communication. As such, gaze behaviour may offer insights into assessing psychiatric conditions in which social communicative difficulties are present, such as ASC. The study of gaze behaviour in psychiatric populations has gained increasing attention in recent years, with studies examining its role in understanding various conditions, including ASC, social phobia, affective disorders and schizophrenia [18–22].

Atypical eye contact is frequently observed in autistic individuals and is recognised as a clinical feature in diagnostic classification systems [1,23]. Studies suggest that autistic individuals process faces differently, directing less attention toward core facial features such as the eyes and nose [24], with a specific reduction in attention toward eyes regions [25,26], and, in some studies, increased attention towards mouth regions, compared to neurotypical controls [24,25]. Meta-analyses corroborate the findings of reduced attention to eye regions in autistic individuals compared to neurotypical counterparts [26–28]; however, findings concerning gaze patterns toward mouth regions remain inconsistent [26,27,29,30].

Beyond feature-specific differences in gaze patterns, autistic individuals also demonstrate a reduced preference for social regions (e.g., faces) compared to non-social regions (e.g., objects) within stimuli [26–29,31]. Meta-analyses report that autistic individuals attend more to non-social regions of presented stimuli and direct less attention to socially relevant areas, such as whole-race regions, relative to neurotypical controls [26–29,31].

However, several moderating parameters within paradigms influence these observed differences. Dynamic stimuli, such as videos, tend to elicit greater differences between ASC and neurotypical groups when compared to static images [28,32,33]. Additionally, social complexity within the stimuli, operationalised as the number of people present, impacts gaze behaviour [17,31,34]. In neurotypical adults, increasing the social content of a stimulus leads to increased fixation time toward social regions, such as eyes and faces [17]. Conversely, autistic individuals exhibit decreased attention to social regions, such as faces and eyes, and increased attention to non-social regions as social content increases [31,34].

Following this, much of the literature is limited due to the reliance on static or simplified stimuli, such as isolated images or videos, which fail to capture the interactive quality of real-world social situations [35]. Passive viewing of stimuli also fails to account for the bi-directionality, or “dual function of gaze” in social situations, where in real-world interactions, gaze functions not only as a method of capturing information but also conveys communicative signals and intent [35]. Gaze behaviour in a paradigm involving passive viewing may, therefore, not represent natural gaze behaviour, challenging the ecological validity of eye-tracking research that does not account for these factors.

Furthermore, a substantial part of the research investigating gaze behaviour in autistic individuals has been conducted in child and adolescent populations, highlighting the need for further studies examining gaze behaviour in adult ASC populations [28,29,31].

The use of virtual reality (VR) provides a promising avenue to counteract these limitations. VR technology enables the creation of highly immersive and complex stimuli resembling real-world situations while maintaining experimental control. Recent studies have demonstrated that participants exhibit stronger reactivity to the gaze of virtual avatars in VR settings compared to traditional laboratory settings, where the stimulus is presented on a monitor [36,37]. Likewise, initial evidence suggests that combining a virtual environment eye-tracking paradigm with a machine learning model can differentiate autistic children from typically developing peers, with high (86%) accuracy and sensitivity (91%) based on differences in attuning to and extracting socially relevant information [38]. This suggests that the use of VR-based stimuli in eye-tracking paradigms has the potential to increase ecological validity and contribute to the current understanding of visual social attention in autistic adults. The current study aims to expand on these preliminary findings by examining gaze behaviour in six computer-generated, immersive social scenarios, investigating whether VR-based eye-tracking can effectively identify group differences between autistic and neurotypical adults.

### Aim

This study aims to investigate the use of VR-integrated eye-tracking to assess gaze patterns in virtual social situations among autistic adults. More specifically, we intend to ascertain whether VR-based gaze patterns reveal group differences between autistic individuals and their neurotypical counterparts.

### Hypotheses

In line with previous findings [18,28,29,31–33], we hypothesise that:

1) Autistic participants will exhibit fewer fixations and shorter dwell time on eye regions of avatars compared to neurotypical participants across the experimental tasks.2) Autistic participants will exhibit different gaze behaviours, such as fewer fixations and shorter fixation duration (dwell time) on social areas (head and body) of the avatars presented in the virtual reality (VR) scenarios compared to neurotypical participants. Additionally, we hypothesise that the number of fixations, mean fixation and dwell time will be greater on non-social areas (objects and surroundings) among autistic participants across the experimental tasks.3) Increased social complexity across conditions, operationalised as a greater number of avatars present, will result in an increase in the number of fixations, mean fixation time, and dwell time on non-social areas among autistic participants compared to neurotypical controls.

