### Experimental paradigm

The experimental paradigm consists of six computer-generated social scenarios simulating a pedestrian street presented in virtual reality. Within each scenario, one avatar approaches the participant and initiates a 19-second interaction. The scenarios vary along two parameters: social complexity, operationalised as the number of avatars present in the background (0, 5, or 25), and the presence or absence of a non-social distractor (an ambulance in the background).

The virtual environment consists of a pedestrian street featuring elements such as buildings with large shopping windows, benches, and a large tree. The duration of each scenario is 90 seconds. When entering the scenario, participants are positioned centrally within the street, facing the same direction each time. Participants can orient themselves while remaining stationary within the environment, i.e., they are unable to perform any locomotion. In each scenario, after 30 seconds, an interlocutor avatar emerges from a passage to the right of the participant’s initial orientation and approaches them. The interlocutor stops directly in front of the participant, adjusting to account for the participant’s physical orientation within the virtual space. Once stopped, the avatar engages in a 19-second interaction involving an initial, neutral question, a brief pause allowing the participant to respond, and a neutral concluding remark (see Table 1 for an overview of the interactions). Following the interaction, the avatar exits the walking street down a passage located behind the participant’s original physical orientation. The avatars are distinct across scenarios, featuring three male and three female characters. All interacting avatars display consistent conversational body language and attempt to maintain eye contact. The scenario concludes after a total of 90 seconds.

**Table 1 pone.0316502.t001:** Overview of avatar interactions.

Initial question	Response
Hi, I couldn’t help but notice your shoes – they’re really nice! Where did you get them?	Thanks – I’ll have to see if I can find a pair like that.
Hey, could I borrow your phone? I can’t find mine – I think I might’ve left it on the bus.	Oh wait, maybe I left it at the café. I’ll just check.
Excuse me, do you know what time it is? I’ve got to catch my movie at the cinema.	Oh, I’d better hurry – it’s starting soon, and my friends are waiting for me.

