Hi, could you point me in the direction of City Hall? It’s my first time here.	I’m so bad with maps; I’ll see if I can figure it out.
Hi! I’m from Animal Protection. Do you have a moment?	Thanks for your time – we’re holding a big event next week. You can read more about it on our website.
Hey there – don’t we know each other? Didn’t we meet at Line’s New Year’s party?	Oh no, I’m sorry! I thought you were someone else – have a great day!

Across the six scenarios, two parameters are manipulated: social complexity and the presence of non-social distractors (see Table 2 for an overview of conditions for each scenario). Social complexity is operationalised as the number of avatars present in the background of each scenario, as this has been found to be a moderating factor when comparing gaze behaviour between ASC and neurotypical groups [31–33]. Three conditions comprise this parameter: *1.* Low social complexity, with no avatars present within the background; *2.* Moderate social complexity, with five avatars walking in the background of the pedestrian street; *3.* high social complexity, with 25 avatars walking in the background on the pedestrian street. The second parameter, non-social distractors, is manipulated through the presence of an ambulance in half of the scenarios, as previous findings suggest that autistic individuals show preferential attention toward non-social objects in a visual scene [46–48].

**Table 2 pone.0316502.t002:** Experimental conditions.

	Non-social distractor absent (Absent conditions)	Non-social distractor present (Present conditions)
**Low social complexity** **(0 background avatars)**	Scenario 1	Scenario 4
**Moderate social complexity** **(5 background avatars)**	Scenario 2	Scenario 5
**High social complexity** **(25 background avatars)**	Scenario 3	Scenario 6

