### Outcome measures

Outcome measures are gaze behaviour analysed through fixation-based metrics including number of fixations, mean fixation time in milliseconds, and dwell time in milliseconds on predetermined Areas of Interest (AOI). Areas of interest are predefined and categorised as social and non-social stimuli. Within social stimuli, AOIs are further categorised to include head, eye, mouth, forehead, and body regions of avatars. AOIs within non-social stimuli will consist of shopping windows, the ambulance when present, and the remaining background. Exploratory outcome measures are associations between eye movement data and clinical, social functioning, and social cognitive measures.

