### Sample size calculation

Sample size was determined a priori based on one of the primary hypotheses of detecting a between-group difference in total fixation duration (dwell time) on the eye regions. The minimal detectable effect size as set at Hedges’ g =  0.47, as established by Frazier et al.’s 2017 meta-analysis [28]. An allocation ratio of 0.35 was selected due to clinical availability to a cohort of participants with ASC [39] and anticipated greater heterogeneity in gaze behaviour within the ASC group [66].

Assuming a two-sided hypothesis with a significance level of 0.05 and statistical power of 80%, the sample size calculation indicated 139 and 48 NT participants. To account for potential attrition, we will recruit 140 ASC and 50 NT participants.

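### For dwell time and fixation counts, the Hypothesis 3 test confounds social complexity with how long any avatar is available to look at

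*Protocol article*

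**What the plan says.** Hypothesis 3 (Protocol article, Hypotheses) predicts that raising the number of avatars leads to "an increase in the number of fixations, mean fixation time, and dwell time on non-social areas among autistic participants compared to neurotypical controls". Hypothesis 2, in the same section, already expects more non-social gaze in the autistic group across all tasks.

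Outcome measures fixes the metrics as fixation counts plus "mean fixation time in milliseconds, and dwell time in milliseconds on predetermined Areas of Interest". Whatever is not avatar, shop window or ambulance falls into a remaining-background area, so gaze is either social or non-social.

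Under Experimental paradigm every scenario lasts 90 s. "In each scenario, after 30 seconds, an interlocutor avatar emerges from a passage"; the avatar then approaches, interacts for 19 s and leaves. The lowest complexity level is defined as "Low social complexity, with no avatars present within the background"; the other two have 5 and 25 avatars walking in the background.

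Statistical analyses tests Hypothesis 3 with a MANCOVA on group, complexity and area of interest. The ASRS score is the only covariate named. No common time window and no adjustment for avatar availability is stated.

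**The concern.** With no background avatars, there is nothing social to look at until the interlocutor appears, and again once it has gone. During that time both groups can only look at non-social areas, so any group difference is forced to zero. Adding 5 or 25 background avatars changes two things at once: how crowded the scene is, and for how long a person can be looked at. A stable group difference in preference has longer to show itself in the crowded scenarios, and the group gap in seconds or counts grows for that reason alone.

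A significant group-by-complexity interaction could then be taken as evidence that autistic adults respond differently to complexity, when only the opportunity to look at people has changed. The bias runs in the hypothesised direction relative to controls, so it would look like confirmation. If Hypothesis 2 is true, Hypothesis 3 is not a separate test.

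**Working it through.** **The plan's own figure.** Sample size calculation uses two-sided alpha 0.05, 80% power, an allocation ratio of 0.35 and this effect: "The minimal detectable effect size as set at Hedges’ g = 0.47". The normal approximation gives n(ASC) = (1 + 1/0.35) × (1.960 + 0.842)² / 0.47² = 137.05, rounded up to 138, and 0.35 × 138 = 48.3 controls. The noncentral t gives 139 and 48.65. The article's statement that "the sample size calculation indicated 139 and 48 NT participants" is reproduced. That figure covers a main effect on eye-region dwell, not the interaction examined here.

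**Availability.** Let W be the seconds in which at least one avatar can be looked at.
- 0 background avatars: at most 90 − 30 = 60 s, and at least the 19-s interaction. Approach and exit times are not given, so W is shown as a range.
- 5 or 25 background avatars: taken as 90 s. This is an assumption; the article implies it but does not state it. The ratio to low complexity is then 90/60 = 1.5 to 90/19 = 4.7.

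**Formula.** Let p be the share of available time spent on avatars, constant over complexity within each group, and let metrics be summed over the whole scenario.
- Non-social dwell = 90 − W × p
- ASC-minus-control gap = W × (p_NT − p_ASC)
- Interaction, 5 or 25 versus 0 avatars = (90 − W) × (p_NT − p_ASC)

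Two assumed pairs of preferences are used: 0.60 versus 0.50, and 0.50 versus 0.43. The second pair is a 0.47 SD gap with an assumed between-person SD of 0.15: 0.50 − 0.47 × 0.15 = 0.43.

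| W at low complexity | Gap low, 0.50/0.43 | Gap 5 or 25 | Interaction | Interaction, 0.60/0.50 |
|---|---|---|---|---|
| 19 s | 1.33 s | 6.3 s | 4.97 s | 7.1 s |
| 30 s | 2.1 s | 6.3 s | 4.2 s | 6.0 s |
| 45 s | 3.15 s | 6.3 s | 3.15 s | 4.5 s |
| 60 s | 4.2 s | 6.3 s | 2.1 s | 3.0 s |
| 90 s (equal availability) | 6.3 s | 6.3 s | 0 | 0 |

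**Direction.** With 0.60/0.50 and W = 60 s, non-social dwell goes from 60 to 45 s in the autistic group and from 54 to 36 s in controls. It falls in both, by 15 s and 18 s; the interaction is the 3-s difference.

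**False-interaction rate.** 4,000 simulated trials per setting were run with 140 versus 50 participants, the 0.50/0.43 pair and no change in preference with complexity. A t-test compared the groups on the within-person contrast (mean of moderate and high minus low). Covariate, distractor and separate areas of interest were left out. Rejection on raw dwell, by assumed within-person SD of the preference:

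| W at low complexity | SD 0.05 | SD 0.10 | SD 0.15 |
|---|---|---|---|
| 19 s | 77% | 67% | 55% |
| 30 s | 76% | 62.5% | 44% |
| 45 s | 70% | 47% | 30% |
| 60 s | 54% | 26% | 16% |
| 90 s | 4.5% | 4.8% | 5.2% |

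- Share of avatar-available time: 4% to 6% in every setting.
- Share of the 90-s scenario, W from 19 to 60 s: 15% to 78%, so no improvement.
- No group gap, SD 0.10, raw dwell: 4.7% (W = 19 s) and 5.1% (W = 60 s).

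A second set of assumptions (between-person SD 0.2, within-person SD 0.1 to 0.2, W = 40 to 60 s) gave 17% to 64% on raw dwell and 5% to 6% on share of available time.

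**The case against.** Several objections have force.

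- **Complexity is the number of avatars, so more opportunity to see people is part of the manipulation.** True, but Hypothesis 3 is motivated by a shift in attention as social content rises, and the planned contrast cannot separate that shift from longer exposure.
- **The article does not say that metrics are summed over 90 s, nor that background avatars are in view throughout, and an unseen analysis plan may set a window.** This stands as a condition on the point. Still, the article itself fixes the outcome units, the hypothesis and the model, and none of them deals with availability.
- **The rates rest on assumed variances, and the 0.47 is borrowed from eye-region dwell.** Correct; they illustrate scale and are not predictions.

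A reader might also infer more than the document supports:

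- That raw milliseconds are the fault. All scenarios last 90 s, so a percentage of scenario time carries the same artefact, and so does valid tracked time over the whole scenario when tracking is near complete.
- That autistic participants would appear to turn towards non-social areas. Under this mechanism their non-social dwell falls, only by less than in controls.
- That unequal tracking loss biases Hypotheses 1 and 2. The article reports no loss rates and does not say that lost samples count as not looking, so that claim has no basis here.

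**Conclusion.** The point holds for dwell time and number of fixations in the contrast of 0 with 5 or 25 background avatars. For counts it assumes that fixations accrue roughly in proportion to time. It rests on three conditions: metrics cover the whole scenario, background avatars are available for longer than the interlocutor alone, and the groups differ by a constant social preference. Hypothesis 2 predicts the third; without it the test keeps its 5% level.

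Under these conditions the spurious interaction is about 2 to 7 s of dwell, and the illustrative false-interaction rate is 16% to 77%, against about 5% on avatar-available time. It would be wrong to extend this to every Hypothesis 3 metric or every step in complexity: mean fixation time is not directly proportional to exposure, and on-screen duration does not confound 5 versus 25 avatars if both run for the full scenario.

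**What to change.** Before analysis, specify for Hypothesis 3 one or both of the following:

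1. Express dwell as a share, and fixations as a rate, of the time in which at least one avatar is available, with numerator and denominator both restricted to that time.
2. Test the hypothesis within the interaction window, which has the same length in all six scenarios and always contains a social target.

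Report whole-scenario raw values descriptively. Claim an increase on non-social areas only if the change within the autistic group is itself positive, and otherwise describe the result as relative to controls. State how long background avatars are present and when the interlocutor arrives and leaves.

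The cost is extra processing of recorded gaze data, with no new data collection. The interaction window also gives a shorter, noisier measure that leaves out free viewing and so asks a narrower question; the availability-scaled measure keeps the free viewing in which an avatar is present.
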